## Plans to promote participant retention and complete follow-up {18b}

Outcome self-report measures will be completed online so that participants may access them at convenient times and places. Participants will receive automated assessment survey invitations and reminders. Dedicated staff members (see Sect. 19) will review participants’ responses and send reminders by email or text if assessment surveys are not complete, until the completion of the assessment period. A database checklist will be available to ensure that all measures are being collected according to the schedule. Participants will also receive a 25€-worth gift voucher for their full participation, at the 6-month follow-up.

Irrespective of intervention discontinuation or deviation from protocol, outcomes data collection will continue for all participants. A variable representing the extent of treatment completion (number of sessions attended) will be added, and sensitivity analyses to evaluate its impact on intervention outcomes will be performed.

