#### Analyses by aims

Aim 1: Determine the efficacy of the Mind programme compared to an active (i.e. support group) and/or inactive (i.e. treatment as usual group) control condition at post-intervention and at 6-month follow-up period.

The planned analysis for each outcome is a repeated-measures linear mixed model, including polynomial simple slopes to identify non-linear change over time. Within-group and contemporaneous between-group post hoc comparisons, using independent- or paired-samples *t*-tests (as appropriate), adjusted for multiple comparisons using the modified Bonferroni adjustment, will be performed. The efficacy of the intervention can be inferred through the evaluation of the simple slopes for each treatment condition, whereby the experimental condition demonstrates a significant improvement in QoL scores over time, and this improvement exceeds that of the control condition. The clinical significance of changes presented by each participant will be determined by computing the reliable change index (RCI) and considering mixed models of repeated measures (i.e. growth modelling analysis). In the former, we will calculate primary or secondary outcome RCI for each participant between pre- and post-intervention, as well as pre-intervention and 6 months. An RCI of ± 1.96 is considered statistically significant at *p* = 0.05, and the proportions of participants within each treatment condition who demonstrate significant improvement, decline and no change will be recorded. Fisher’s exact test will be used to examine for significant differences in the proportion of change between treatment allocations. Finally, we will perform correlation analysis between the raw RCI values and demographic variables separately for each treatment condition. This final analysis is used to examine potential predictors of individual change and the nature of that change.

Aim 2: Determine the cost-effectiveness of the Mind programme compared to an active (i.e. support group) and/or inactive (i.e. treatment as usual group) control condition at post-intervention and at 6-month follow-up period.

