### Methods in analysis to handle protocol non-adherence and any statistical methods to handle missing data {20c}

All main analysis will be performed as an intention-to-treat (ITT) analysis to provide unbiased estimates of the intervention efficacy regarding the level of participants’ adherence to the study. In such an approach, the participants will be considered according to the group they were originally assigned to regardless of intervention compliance. Missing data will be reported and when MCAR (Missing Completely at Random) or MAR (Missing at Random) occurs, multiple imputation methods will be used to estimate missing values when appropriate. Missing values will be imputed with well-established methods that reduce bias in estimates such as multiple imputation, full information maximum likelihood and empirical Bayes estimation, or multiple imputations with chained equations (MICE), if a substantial amount of missing data exists.

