### Interim analyses {21b}

These are low-risk behavioural intervention studies and they were preceded by a pilot study which provided preliminary safety data [29]. Although unlikely, adverse events and clinically significant deterioration will be monitored, discussed and reported (see Sect. 22), following recommendations [61]. The lead statisticians will look for clinically significant deterioration on any outcome at the midpoint of the trials. Clinically significant deterioration will be determined through RCI analyses from baseline to the immediate post-treatment. If clinically significant deterioration is detected, a standardised procedure will follow (see Sect. 22).

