### Adverse event reporting and harms {22}

Although unlikely, given the behavioural nature of the interventions and the preliminary data on safety [29], adverse events and clinically significant deterioration will be monitored, discussed and reported, following recommendations [61].

Adverse events and other unintended effects of the trials will be monitored by the therapists of each intervention group. Possible adverse events are as follows: clinically relevant increases in psychological distress, from heightened emotional reactions when confronting difficult thoughts or memories; relevant physical complaints/discomfort (e.g. headaches, muscle tension) from practising unfamiliar exercises, such as the body scan exercise; interpersonal conflict that is disruptive to the group functioning.

Participants will be encouraged to self-report deterioration since the start of the interventions and lead statisticians will look for clinically significant deterioration on any outcome at the midpoint of the trials (see Sect. 21b).

The occurrence of adverse events or clinically significant deterioration will be reported to the involved Ethics Committees and to the SC (see Sect. 5d), who will determine whether they are likely to be related to the intervention and may give recommendations to the PI for the early termination of the trials. The PI has the ultimate authority over early termination, but she will be guided by Linden and Schermuly-Haupt’s [62] stopping rule: if related adverse events or clinically significant deterioration are observed in 20% (approximate base-rate for adverse events in psychotherapies) of the intervention cohort by the trial midpoint, the study will be terminated.

Participants who experience treatment adverse effect or related clinically significant deterioration will be unblinded, removed from the study and provided with appropriate healthcare. As stated before (see Sect. 30), there are no provisions for any additional post-trial care or to provide compensation to those who suffer harm from trial participation.

All adverse events and clinically significant deterioration will also be reported in the trials’ scientific outputs.

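### The harms section removes harmed or deteriorated women from the study, while the retention section promises outcome data from everyone; the resulting loss depends on outcome and can bias the effect in either direction

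*Protocol article*

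**What the plan says.** Section 22 (adverse event reporting and harms) says: "Participants who experience treatment adverse effect or related clinically significant deterioration will be unblinded, removed from the study and provided with appropriate healthcare". It does not say whether these women still receive the post-treatment and 6-month questionnaires.

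Section 18b (retention) says: "Irrespective of intervention discontinuation or deviation from protocol, outcomes data collection will continue for all participants". It makes no exception for harm.

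Section 20c makes the main analyses intention-to-treat, so that "the participants will be considered according to the group they were originally assigned to regardless of intervention compliance". For missing values, "when MCAR (Missing Completely at Random) or MAR (Missing at Random) occurs, multiple imputation methods will be used to estimate missing values when appropriate".

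Section 21b explains how deterioration is found: "The lead statisticians will look for clinically significant deterioration on any outcome at the midpoint of the trials", and "Clinically significant deterioration will be determined through RCI analyses from baseline to the immediate post-treatment". Section 22 adds two other routes to detecting harm: monitoring by the therapists of the intervention groups, and self-report by participants.

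The reliable change index (RCI) is also an efficacy analysis. Under Aim 1, "An RCI of ± 1.96 is considered statistically significant", and the proportions in each arm "who demonstrate significant improvement, decline and no change will be recorded".

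**The concern.** The sections give staff opposite instructions. Someone following section 22 would stop sending questionnaires to a woman removed for harm; someone following section 18b would keep sending them. It cannot be assumed that removal from the study only means leaving the group sessions. Section 11b treats opting out of the intervention and opting out of the studies as different things, and section 11a keeps women who miss sessions in the trial and in the intention-to-treat analysis.

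The loss would not be random. The RCI check covers any outcome, the primary included, and the adverse events listed in section 22 include clinically relevant increases in distress, which lie close to the HADS scales and to QLQ-C30 emotional functioning. A woman would therefore leave because her outcome was poor. That undermines the intention-to-treat claim at 6 months. It could also understate the number of women counted as declined in the 6-month RCI comparison.

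**Working it through.** **Yardstick.** The protocol gives no figure for bias from removal. The nearest stated figure is study 1's detectable SMD of 0.51. It follows from (1.960 + 0.842) × √(2/n) with n = 60 per arm, which gives 0.51. Here n = 60 is 75 less 20% attrition; the 20% is my assumption, the midpoint of the stated 10–30%. Study 2 assumes an SMD of 0.5 against waiting list.

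**Inputs from the protocol.** Three assessments with compound-symmetry correlation 0.5 (section 14, study 1); Cronbach's alpha 0.88 for global QoL, with subscales from 0.57 (section 18a); RCI cut-off 1.96 (section 20a).

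**Assumptions.** Normal scores with SD 1; the Aim 1 cut-off also defines deterioration; alpha serves as the reliability in the RCI; every flagged woman is removed; a between-arm difference present at post-treatment persists to 6 months.

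**Share flagged.** The cut-off on the change score is -1.96 × √(2 × (1 - 0.88)) = -0.96 SD. The change from baseline has variance 2 × (1 - 0.5) = 1. With mean change m, the share flagged is Φ(-0.96 - m): 16.9% at m = 0, 11.3% at m = 0.25 and 7.2% at m = 0.5.

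**Lift if the women are dropped entirely.** The post-treatment and 6-month changes correlate at 1 + 0.5 - 0.5 - 0.5 = 0.5. Removing women with change below the cut-off raises the arm's mean 6-month change by 0.5 × φ(a)/(1 - Φ(a)), where a = -0.96 - m:

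- m = 0: 0.5 × 0.2516/0.8315 = 0.151
- m = 0.5: 0.5 × 0.1374/0.9279 = 0.074
- m = -0.25: 0.5 × 0.3100/0.7612 = 0.204

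The bias is the Mind lift minus the control lift, for example 0.074 - 0.151 = -0.08. A simulation with one million women per arm gave the same values. It also covered two milder readings: only the baseline score is kept, or baseline and post-treatment scores are both kept and analysed under missing at random.

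| Scenario | Dropped entirely | Baseline kept | Baseline and post-treatment kept |
|---|---|---|---|
| Same rule, equal change | 0.00 | 0.00 | 0.00 |
| Same rule, Mind better by 0.5 | -0.08 | -0.05 | 0.00 |
| Same rule, Mind worse by 0.25 | +0.05 | +0.03 | 0.00 |
| Mind only loses women, no true effect | +0.15 | +0.08 | 0.00 |
| Mind only loses women, Mind better by 0.5 | +0.07 | +0.04 | 0.00 |

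**Sensitivity.** If only half of the flagged women are removed in each arm and Mind is better by 0.5, the -0.08 becomes -0.03. With reliability 0.57 the cut-off is -1.82 SD, 3.5% are flagged at m = 0, and the one-sided null case falls to 0.5 × 0.0765/0.9654 = +0.04.

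**If outcomes are still collected**, as section 18b promises, this selection bias is zero in every scenario.

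**The case against.** The strongest case on the other side is that this is a wording conflict about events the protocol expects to be rare, and that the damage is limited. Several parts of it stand.

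- A reader might infer that these women's data are deleted from the arms. The text does not say so. It nowhere discards collected data or takes the women out of the intention-to-treat set; at most, later assessments are at risk.
- A reader might infer that the bias must favour Mind in both trials. It need not. Study 1 compares two therapist-led groups of the same format. If the rule works alike in both and Mind helps, the control arm loses more women and the bias is nil or against Mind.
- A reader might take 20% as the expected removal rate. In section 22 it is an approximate base rate used as a stopping threshold, so a trial reaching it by the midpoint would be terminated.
- Only a treatment adverse effect or related deterioration triggers removal, and the ethics committees and steering committee judge relatedness. The RCI check is made at the trial midpoint. Both narrow the loss.
- Detection is not left to therapists alone. Self-report and the RCI check are not stated to be confined to the therapist-led arms.
- For cases found by RCI, the post-treatment score already exists. If it is kept, a likelihood analysis under missing at random showed no bias.
- Section 22 promises that all adverse events and deterioration will be reported, so harm would not disappear from the publications.

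What the objection does not remove: the two instructions still conflict. A therapist's observation or a self-report can lead to removal before any post-treatment score exists, and then the missing-at-random repair lacks the score it needs. Treatment-as-usual women receive no trial intervention, so they can hardly have a related event, and a one-sided loss in that contrast is plausible.

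**Conclusion.** The point holds as a contradiction between sections 22 and 18b that puts the intention-to-treat statement in section 20c at risk. It does not hold as a claim of deleted data or of a known upward bias.

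Under the scenarios above, bias in the 6-month SMD lies between about -0.08 and +0.15. The upper end is 0.15/0.5 = 30% of the effect assumed in study 2, and it needs one-sided removal, no true effect and the women dropped entirely. Upward bias is most plausible against treatment as usual. Between the two active arms it is about nil if they lose women equally, nil or downward if Mind works, and upward if Mind does worse. The 6-month decline counts may be understated in any arm that loses women.

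These sizes are illustrations. They rest on normal scores, correlation 0.5, reliability 0.88 and removal of every flagged woman. Limiting removal to related cases makes them smaller; checking any outcome, not just one, raises the share flagged. The contradiction itself rests on no assumption.

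**What to change.** Reconcile sections 18b and 22 on outcome collection and the analysis set. State that:

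1. post-treatment and 6-month questionnaires continue for women with a treatment adverse effect or related deterioration, unless they withdraw consent to follow-up;
2. these women stay in their randomised arm for the intention-to-treat analysis, with all data already collected kept;
3. the number and timing of such removals are reported by arm.

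The cost is a short protocol clarification and a notification to the ethics committees. The self-report questionnaires are already completed online with reminders, so little new work is needed. Decisions on treatment, unblinding and care are left to the sponsor, and no clinical rule is proposed here.

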### Frequency and plans for auditing trial conduct {23}

N/A: A formal audit of the trial conduct will not be established. However, the institutional sponsor and the funder might ask/perform a random audit.

### Plans for communicating important protocol amendments to relevant parties {25}

Important protocol modifications will be reported to investigators, participants, ethics committees, funder, trial registries and journals.

### Dissemination plans {31a, 31b}

Trial results will be published in peer-reviewed journals and disseminated in scientific meetings and to the press. No professional writers will be used. Authorship eligibility will be determined by ICMJE’s guidelines [63].

## Discussion

This research comprises two pioneering RCTs aiming to test the superiority of an optimised version of the Mind programme, an integrative ACT and compassion-based intervention tailored for women with BC, in improving psychosocial, biological (i.e. immunological and epigenetic) and economic outcomes, compared to an active (i.e. support group) and/or inactive (i.e. treatment as usual group) control condition.

### Limitations

There are several potential limitations to consider. First, the high risk of participant dropout. Patients may not be available or willing to complete post-treatment or follow-up assessments, despite research team efforts to retain study participation (e.g. regular contact, reminders, gifts). Second, recruiting patients already overwhelmed with BC treatment agenda is challenging. Finally, it is possible that our findings may not be generalised to some groups of women with BC (e.g. patients from remote rural areas or digital naïve patients).

### Strengths

First, the pilot study of the Mind programme supported its methodological implementation, and patient and therapist feedback were used to optimise the intervention. Second, the use of an active control group. Compared to the control group(s), participants allocated to the Mind programme are expected to show a higher degree of improvement in cancer-specific quality of life and depressive and anxiety symptoms. Improvements in these outcomes are expected to lead to a concomitant decrease in miRNAs expression and inflammatory biomarkers, as well as to increased cellular immunity (study 1 only). Also, improvements in primary and secondary outcomes are expected to lead to decreases in healthcare resources consumption and in economic costs associated with BC, in both studies. Third, the analysis of the potential mechanisms of change of the Mind programme is an important aspect of the current research. Changes in cancer-specific QoL in the experimental group are expected to be due to improvements in mindfulness, psychological flexibility and self-compassion, and to be maintained over the follow-up assessment, especially in participants that continue mindfulness and compassion practice (prescribed for between-session practice) post-intervention. It is also possible that each intervention will be distinctively beneficial or particularly efficacious for certain subgroups of patients (e.g. higher in psychological distress severity at baseline, younger). This kind of finding would provide important data for treatment customisation in BC. At last, findings from these RCTs will inform about appropriate methods of supporting women with BC who are undergoing radiotherapy, and potentially have important implications for the integration of psychosocial support to optimise service design, delivery and customisation in this population. Findings will also support future studies that may evaluate the Mind programme or other ACT and/or compassion-based interventions for people with cancer, and potentially highlight the clinical relevance of integrative interventions in oncology.

## Trials status, protocol version {3}

Study 1: Recruitment started in January 2023 and is estimated to be complete by March 2025. The current approved protocol (NCT05642897) is version 4 (date of approval: 2024–01–19).

Study 2: Recruitment started in October 2023 and is estimated to be complete by March 2025. The current approved protocol (NCT06212414) is version 1 (date of approval: 2024–01–15).

## Data Availability

Databases generated by these studies will be made available upon reasonable request to the PI.
